## 4.4 Safety Objectives

The safety of non-contrast syngo DynaCT Sine Spin imaging will be evaluated by documenting all device related AEs and SAEs, which occur during the procedure and within a safety-period of up to 24 hours after the procedure.

# 5. CLINICAL INVESTIGATION OUTCOMES

## 5.1 Primary Outcome

The primary outcome is the occurrence of intracranial hemorrhages (yes vs no) as assessed by a blinded core-lab. The primary outcome will be used to calculate the sensitivity and specificity of non-contrast syngo DynaCT Sine Spin imaging for the detection of intracranial hemorrhages.

## 5.2 Safety Outcomes

All procedure and device related AEs and all Device Deficiencies will be evaluated until 24 hours after the procedure.

# 6. CLINICAL INVESTIGATION DESIGN

## 6.1 General clinical investigation design and justification of design

The clinical investigation is designed as a cross-sectional, non-inferiority trial with prospective open label data collection and blinded endpoint assessment. The intervention to be studied is non-contrast syngo DynaCT Sine Spin. The intervention will be done as in standard of care setting.

The patient population consists of patients with a suspected severe acute ischemic stroke (NIHSS at admission ≥ 7 and time from last seen well maximum 24 hours) or with symptoms suggestive of an intracranial haemorrhage (for example reduced consciousness). All patients will undergo first non-contrast MDCT imaging and then afterwards non-contrast syngo DynaCT Sine Spin imaging. As the study is designed to be cross-sectional, there is no control group. All patients will undergo the same procedures. Only patients in whom no invasive intervention is planned between both scans and in whom it is feasible to perform both scans within a time-period of up to four hours can be enrolled. This time span however is assumed to be far shorter in many patients (especially in mothership patients; most likely under 30 minutes). The total duration of the intervention itself will be 7 seconds scan time and up to 1 minute procedure time (not including positioning of the patient). Patient positioning is done independently from the participation in the proposed clinical investigation. The total duration of the clinical investigation for each patient will be up to four hours from enrolment to the last assessment. There is no further follow-up visit planed after the sine-spin non-contrast FDCT.

Patients will be enrolled after the non-contrast MDCT and best medical therapy. This approach was chosen as enrolment prior to the non-contrast MDCT, and best medical therapy would lead to inacceptable time delays in this patient cohort. Based on clinical symptoms and imaging findings of the non-contrast MDCT patients can be enrolled in one of three buckets: (1) acute ischemic stroke patients, (2) patients with an intracranial haemorrhage which has supratentorial portions and (3) isolated infratentorial or basal intracranial haemorrhages (including perimesencephalic SAH). In total 252 patients will be enrolled (for justification of sample size see section 11) and they are distributed over the buckets in the following proportions:

- Bucket 1 (acute ischemic stroke patients) 126 patients
- Bucket 2 and 3 (haemorrhage patients) 126 patients including 14 patients in bucket 3 (isolated infratentorial or basal intracranial haemorrhage including perimesencephalic SAH)

Local investigators must keep a screening log.

The primary objective (sensitivity and specificity of non-contrast syngo DynaCT Sine Spin imaging for the detection of intracranial haemorrhage) will be assessed by blinded readers in an imaging core-lab. All readers will be blinded to all clinical characteristics and will not be involved in the treatment or enrolment of patients. Prior to the core-lab assessment all scans will be anonymized, reconstructed in a standardised way (fixed angles and slide sizes) and randomized. All readings will be noted on standardized forms.

The ground truth (i.e., if an intracranial haemorrhage is present or not) will be defined based only on the MDCT scans according to the following procedure: If the reading of the clinical reader (the enrolling physician at the participating site) and the reader from the first blinded core-lab (provided by the Neurovascular Imaging Research Core, [name], University of California LA, Los Angeles, California, USA) is consistent this will be deemed as ground truth. If they are inconsistent a second core-lab (provided by [name], Inselspital Bern, Bern, Switzerland) will make a final ruling (majority vote). The second core-lab can use all available clinical information but will be blinded to the results of the reading from core lab one. The following table illustrates the definition of the ground truth:

| Modality | Reader | Analysis |
| --- | --- | --- |
| MDCT | Clinical Reader | Agreement: ground truth |
|  | Core-Lab 1 | Disagreement: Unblinded expert reader in 2^nd^ corelab determines ground truth (majority vote) |

Table 1: Definition of the ground truth

The FDCT readings of the six core-lab readers will be compared with the ground truth and based on this comparison they will be rated as true positive, true negative, false positive or false negative. This will be done separately for each reader. In case most of the first core-lab readers (at least 5 out of 6) detect a hemorrhage on the FDCT scan, which according to the ground truth was no present on the MDCT scan, the second core-lab will use all available images and clinical data (unblinded) to decide if there is any evidence for the hemorrhage to have occurred between the MDCT and FDCT scans (always a possibility in patients with a stroke, e.g., without a hemorrhage on MDCT, treated with iv-lysis and then with a hemorrhage on FDCT as a complication of intravenous lytic treatment). In this case the patient will be excluded from further analysis. See table 2 for a detailed overview of all possible constellations:

| Ground truth | Core-Lab 1 | Core-Lab 2 | Final Result |
| --- | --- | --- | --- |
| MDCT | FDCT | FDCT | FDCT |
| (+) | (+) | NA | True (+) |
| (-) | (-) | NA | True (-) |
| (+) | (-) | NA | False (-) |
| (-) | (+) | (-) | False (+) |
| (-) | (+) | (+) | Hemorrhage occurred between scans |

Table 2. Overview of possible outcomes for the FDCT readings

Based on the results the sensitivity and specificity of non-contrast syngo DynaCT Sine Spin for the detection of hemorrhages will be calculated.

We chose this design approach for the following reasons:

1. The only way to benchmark the diagnostic performance of non-contrast syngo DynaCT Sine Spin imaging for the detection of intracranial haemorrhage is to compare it to the gold standard, which is cranial non-contrast MDCT imaging.^19, 44^ Therefore, it is of pivotal importance that scans of the same person, which were acquired under comparable conditions are used. This is ensured by the facts that (a) only patients in whom no invasive procedure between both scans is planned can be enrolled and (b) that the time period between both scans is under four hours. Using these criteria, it is highly unlikely, that new bleeding events occur between both scans. However, to account for the very low possibility of an early bleeding due to intravenous lysis, which would occur after the MDCT but before the FDCT, a second core-lab was implemented to identify these cases.

2. Although patients will be enrolled based mainly on clinical features, we defined a required number of patients (n = 14) with bleedings which are according to current literature harder to detect on predecessor FDCT generations than on MDCT, i.e. isolated bleedings in the posterior fossa / isolated infratentorial hemorrhages.^39, 48^ This approach was chosen to estimate the diagnostic performance of non-contrast syngo DynaCT Sine Spin imaging also in challenging, rare cases. It therefore allows a broader estimate of its ability for the detection and exclusion of intracranial hemorrhages. However, for the final analysis these cases will have a lower weight as they would have if they were count in by their proportion (14 isolated infratentorial bleedings out of 126 bleeding cases: 11%). In the final analysis they will contribute to the estimate of the sensitivity for the detection of intracranial hemorrhage of FDCT with a fixed weight of 2% (please refer to section 11.5 for a detailed description of the primary analysis). This weight which is lower than their share within the sample size was chosen as from the principal investigators and the US chairs clinical experience (including over 30 years of attending work in neuroradiology/neurosurgery) these cases are very rare (< 1%) in the investigated population and rarely present with symptoms, which would lead to a direct to angiography approach. To further validate their estimated prevalence in the patient group of question (patients with symptoms suggestive of an acute ischemic stroke), we did an analysis of all suspected stroke cases presenting to the University Hospital Basel in the years 2015 to 2019. The data was derived from the Swiss Stroke Registry and included 5,448 patients. Out of these only 48 patients (0.8%) presented with an isolated infratentorial bleeding.

The decision to include 14 isolated infratentorial / posterior fossa bleedings was chosen to be able to generate meaningful data for this bleeding type as well. It assumes that the sensitivity for the detection of these bleedings is 70%. In this case we would have a power of 80% to show that the lower bound of the corresponding 95%-CI interval of the sensitivity for these cases is above 50%. Please refer to section 11 for a detailed description of the calculation of the sample size.

3. Due to the nature of the intervention the enrolling physician and patients cannot be blinded to the intervention. Therefore, we opted for a blinded assessment of the endpoints to minimize bias. All readers in the first core-lab, who will assess the main endpoint will be blinded to all clinical data and will not participate in the enrollment of patients. In addition, a time-limit of 90 seconds per FDCT scan will be implemented to simulate real life conditions as in normal clinical practice the detection of intracranial hemorrhage often happens under considerable time pressure. The readers of the MDCT and FDCT scans will not be the same physicians and they will not share any information.

4. The non-inferiority approach was chosen to generate meaningful clinical evidence regarding the diagnostic abilities of non-contrast syngo DynaCT Sine Spin imaging. Non-inferiority trials for the evaluation of diagnostic modalities were done multiple times in different fields, highlighting the high value of these trials.^49, 50^ The non-inferior thresholds were derived from expert statements from highly experienced neuroradiologists/neurosurgeons.

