## 1.9 Secondary Imaging Core Lab (ICL)

The objective of the second ICL is to make a final ruling a) in case there is a disagreement in the clinical rating and the first core-lab rating of the MDCT or b) in case the majority of the first core-lab ratings (at least 5 out of 6) of the FDCT is hemorrhage positive and the ground truth is hemorrhage negative, to determine if the hemorrhage has occurred between both scans. The second ICL will be blinded to the rating of the core-lab 1 but not to the remaining clinical data. The second ICL defines the ground truth for all patients in whom the clinical rating and the rating of core-lab 1 of the MDCT are divergent (majority vote).

The second ICL will be performed by [name], MD (Head of the Clinic for diagnostic and interventional Neuroradiology, University Hospital Bern), who is an internationally known Neuroradiologist with more than 20 years of experience in the assessment of cranial non-contrast images in stroke patients. All readings will be done in accordance with a core-lab manual, which will be written prior to any assessment. As the second ICL will not be blinded to any data (except to the readings of the first ICL), it is not a problem that [name], MD might have been involved in the original enrollment of patients at the study site Inselspital Bern, Bern, Switzerland.

[name], MD

Head of the Clinic for diagnostical and interventional Neuroradiology

University Hospital Bern

[name]

[name]

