It was tested whether the lower end of the 95%-CI did not fall below the prespecified margins. For sensitivity and for specificity this was 95%. The 95%-CI of sensitivity and specificity were calculated by fitting a generalized linear random-effects model with a logit link function. Random-effects variables were patient and reader, outcome variable was the randomly generated binary vector. To converge to model estimates, the algorithm of the “nloptwrap”-optimizer was applied.

From the model, the lower end of the 95%-CI of the fixed-effect intercept was extracted and transformed to percent. The 95%-CI was calculated by the method of Wald. If the lower ends of the 95%-CIs of sensitivity and specificity both did not fall below a pre-defined margin, the experiment was rated as “successful”. The percentage of “successful” experiment out of all experiments characterizes the study power. Each sample size, n_i=1,..,19_ = 80,…,260 was evaluated by sampling 999 times n_i_ individual samples with a range of readers from 1 to 7.

If the total weight of “difficult cases” is set at 0.02, the number of difficult cases at n= 14, the power at 90% the number of readers at 6, and the drop-out rate at 5%, a total of **252 patients** (238 patients without drop-outs) must be recruited. The patients must be pre-selected in a ratio of hemorrhage positive to hemorrhage negative of 1:1, i.e., 126 patients are presenting with and 126 patients without intracranial hemorrhage (out of which 14 present with an isolated infratentorial intracranial bleeding). The number of readers was set based on our model calculations since with a lower number of readers the sample size fluctuated substantially (over 100%). The needed sample size however stabilized at a range of 5 to 7 readers. With this number of readers, the sample size fluctuated only by 10% (with 7 readers being the lowest and with 5 the highest).

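### Post-result exclusion of consensus FDCT false positives may rest on the same FDCT, which can remove reproducible device errors and raise observed specificity

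*Protocol*

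**What the plan says.** Six readers score each FDCT against a ground truth set from MDCT alone. Section 6.1 adds a second step for one type of discordance: "In case most of the first core-lab readers (at least 5 out of 6) detect a hemorrhage on the FDCT scan" while the ground truth is negative. Then "the second core-lab will use all available images and clinical data (unblinded) to decide" whether there is any sign that the bleed arose between the two scans. If so, "In this case the patient will be excluded from further analysis". The synopsis and sections 1.9 and 9.2 repeat the rule.

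Table 2 in section 6.1 has the column headings "MDCT | FDCT | FDCT | FDCT" (ground truth, core lab 1, core lab 2, final result). Negative / positive / positive maps to "Hemorrhage occurred between scans"; negative / positive / negative maps to a false positive. All other rows show no second-lab entry. The same table in the synopsis heads the second-lab column Unblinded.

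On blinding, section 1.9 states: "The second ICL will be blinded to the rating of the core-lab 1 but not to the remaining clinical data". On how often a new bleed is expected, section 6.1 states: "Using these criteria, it is highly unlikely, that new bleeding events occur between both scans". On the margin, section 11.2 states: "For sensitivity and for specificity this was 95" percent. The full analysis set in section 11.5.1 consists of all patients whose FDCT was rated by the six readers; it does not mention this exclusion.

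**The concern.** The exclusion depends on the index-test result and reaches only the errors that cost FDCT most: patients without hemorrhage whom five or six readers called positive. Two explanations must be told apart, a real bleed that developed after the MDCT and a false signal on the FDCT. If the second lab may rely on the same FDCT, a mimic that misled five of six readers may look like blood again, and the patient leaves the denominator.

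The protocol itself foresees mimics. CT angiography or perfusion may accompany the MDCT (section 9.3.1), readers record whether contrast was present on the FDCT (section 9.2), and Appendix B asks for a description of lesions that imitate bleeding. No study follow-up is planned (section 9.2.6), so independent confirmation is not assured.

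Blinding to core lab 1 gives little protection. An FDCT case reaches the second lab for this question only if at least five readers were positive, so referral itself discloses the consensus.

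At stake is specificity, one of two co-primary quantities whose lower 95% bound must exceed 95%. With an assumed specificity of 98%, few error patients are expected, so one or two exclusions can matter.

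**Working it through.** **Inputs from the protocol.** Margin 95%, 6 readers, assumed specificity 98%, 238 evaluable patients in a 1:1 ratio (119 negatives), 5% drop-out. The between-reader correlation is described as high, without a number (section 11.2).

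**The plan's own figure.** 119 / 0.95 = 125.3, rounded up to 126 per group; 2 × 126 = 252. This reproduces the drop-out step only. The 238 and the 90% power come from a simulation that cannot be rebuilt without the correlation.

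**Direction.** With E false-positive reads among n negative patients, observed specificity is 1 − E/(6n). Removing a patient with f false-positive reads gives 1 − (E − f)/(6(n − 1)). This is larger whenever E/(6n) < f/6. For f = 5 or 6 that holds at any error rate below 5/6. Sensitivity is untouched, because the patient is ground-truth negative.

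**Size.** Take 119 negatives with four error patients having 6, 6, 1 and 1 false-positive reads, 14 of 714 in all. Let p be the mean of the patient proportions pᵢ, with patient-clustered standard error on the logit scale

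SE = √[Σ(pᵢ − p)² / (n(n − 1))] / [p(1 − p)], lower bound = expit(logit p − 1.96 × SE).

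- No exclusion: p = 700/714 = 98.04%; Σ = 2.010; SE = 0.01196/0.01922 = 0.622; logit p = 3.912; bound = expit(2.692) = 93.7%.
- One exclusion: p = 700/708 = 98.87%; Σ = 1.040; SE = 0.00868/0.01117 = 0.777; logit p = 4.472; bound = expit(2.949) = 95.02%.
- Two exclusions: p = 700/702 = 99.72%; bound = 98.9%.

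The first exclusion adds 0.83 points and crosses the margin. The result depends on the pattern. With 6, 6 and 2 (also 14 errors) the bound runs 93.6%, 94.8%, 98.0%, so two exclusions are needed. With six unanimous false positives, excluding four leaves 113/115 = 98.3% and a bound of 93.3%, which still fails.

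**False-pass rate.** Simulated trials (1,500 per cell) used 119 negatives, 6 readers, a true specificity of 95% (the margin) and beta-binomial reads with an assumed within-patient correlation. The same clustered bound was applied, with none, half or all of the consensus false positives removed:

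| Assumed correlation | None removed | Half removed | All removed |
| --- | --- | --- | --- |
| 0.1 | 2.7% | 2.8% | 2.8% |
| 0.3 | 2.6% | 4.7% | 6.1% |
| 0.5 | 2.8% | 7.9% | 26% |
| 0.7 | 2.4% | 12.7% | 63% |

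Repeat runs of the two largest cells gave 24 to 26% and 63 to 66%.

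**Limit of this check.** The clustered bound stands in for the planned mixed model. At a true specificity of 98% and no exclusion it passes specificity in about 91% of trials at correlation 0.1 but about 51% at 0.5, so it does not reproduce the plan's 90% power at high correlation. A simplified patient-only mixed model was unstable with so few errors, and its bound sometimes fell after an exclusion.

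**The case against.** The strongest reply is that the text asks about timing, not for a re-read. The second lab has the MDCT, the FDCT and the clinical record, including thrombolysis, whereas the six readers saw the FDCT alone, blinded, under a 90-second limit. Table 2 has a row in which the second lab rejects the finding and the false positive stands. The synopsis heading does not say FDCT. The rule is pre-specified, its threshold is high so that errors by one to four readers always count, and a manual is to be written before any assessment. All of this stands. A reader might infer that a positive re-read of the FDCT by itself removes the patient; the documents do not say that. They permit it, because no other evidence is required and one table points that way.

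The one-sided trigger also follows partly from the scan order. MDCT comes first, so a bleed can appear in the interval but is not expected to vanish. That answers why positives are reviewed. It does not answer why the FDCT under test may supply the evidence.

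A bleed missed on MDCT could receive the same label. There FDCT was right, and counting it as an error would bias specificity downward. This is a fair reason to show results both ways.

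The missing mention in section 11.5.1 might be read as a contradiction. It is an omission to align, since sections 6.1 and 9.2 state the exclusion clearly.

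**Conclusion.** The concern holds as a bias risk in a pre-specified rule, and it should be fixed. Observed specificity rises by about 0.8 points per excluded patient at 119 negatives, and in a plausible read pattern one exclusion carries a clustered lower bound across 95%. The effect on the false-pass rate is nil at correlation 0.1 and substantial at 0.5 to 0.7. The protocol calls its correlation high, but both the correlation values and the share of consensus cases excluded are assumptions here. No passage supports a particular misclassification rate for the second lab.

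Two stronger conclusions are not supported. One is that the confidence bound can only rise: this is shown for observed specificity, not for the mixed-model bound. The other is that the rule strips out nearly all information on false positives: in the simulations, consensus cases hold about 36 to 62% of false-positive reads at correlations of 0.5 to 0.7.

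**What to change.** 1. In the primary analysis, exclude such a patient only when the second core lab documents evidence of a new bleed that does not come from the study FDCT alone, for example routine follow-up imaging or the documented clinical course. Otherwise keep the reads as false positives.
2. Report specificity with its 95% CI both with all such patients retained and with the exclusions applied. Give the number excluded and state whether the 95% conclusion holds in both. This is a robustness statement, not a second formal success criterion.
3. Reconcile the Table 2 heading in section 6.1 with its text and with the synopsis table, and state in section 11.5.1 how these patients are handled in the full analysis set.

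The cost is wording in the synopsis and in sections 6.1, 9.2 and 11.5.1, plus one extra reported estimate. The downside is that a genuine new bleed without confirmation counts against FDCT. By the protocol's own account such bleeds should be rare, so the expected loss is small.

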### 3.4.2 Clinical evidence to Date

We screened 4,950 records, out of which one evaluated non-contrast syngo DynaCT Sine Spin for the detection of intracranial haemorrhage.^6^ Furthermore, we found a few publications evaluating non-contrast cranial FDCT imaging in general for bleeding detection.^18, 42, 43^ The two most recent publications found very high sensitivities for the detection of intraparenchymal or intraventricular haemorrhage (97-100%) but only moderate to high sensitivity for the detection of subarachnoid haemorrhages, especially in the posterior fossa.^6, 42^

However, all these studies had important methodical issues. Most importantly, only a minority of patients came from the most relevant patient group: suspected stroke patients presenting with a spontaneous intraparenchymal and/or intraventricular haemorrhage. They mainly used surrogate patients, as they included patients which developed an intraparenchymal and/or intraventricular haemorrhage after an intervention. Findings from these patients cannot be generalized to patients presenting with a spontaneous intraparenchymal and/or intraventricular haemorrhage as haemorrhage location, size and distribution might differ substantially. An analysis of the Swiss Stroke Registry of patients from the University Hospital Basel showed that in our targeted patient population (suspected acute stroke patients with an NIHSS ≥7) 16% presented with such a spontaneous haemorrhage. Secondly, the studies did not define the patient population prospectively but rather used all patients available for their analysis. Therefore, the reported sensitivities and specificities could not be generalized to our targeted patient population (patients presenting with symptoms suggestive of a severe acute ischemic stroke or an intracranial bleeding). Third, in some of their cases an FDCT which was done prior to an intervention was compared to an MDCT which was done after the intervention. In these cases, it is not always feasible to deduce, if a bleeding occurred due to the intervention or was missed in the first scan. Also, due to the retrospective nature of the studies selection bias could not be ruled out.

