## 9.2 Assessments of outcomes

All outcomes will be assessed by a blinded and independent imaging core-lab. For this purpose, all scans will be anonymized, reconstructed in a standardized matter (i.e. fixed slice thickness 5 mm, distance 3 mm and angles - orbitomeatal) and randomized prior to evaluation.

The main core-lab will be provided by the Neurovascular Imaging Research Core at UCLA ([name], University of California Los Angeles, Los Angeles, California, USA). The experience of the Neurovascular Imaging Research Core at UCLA as an imaging and angiography core lab is unrivaled, including more than 15,000 acute ischemic stroke cases treated with endovascular therapies in the last several years.

To ensure compliance with the Protocol and adequate acquisition technique of the FDCT and MDCT at the respective site the first five cases from each site will be deemed as lead-in cases. Cases can be excluded and deemed as Screen Failures if they show clear evidence of (a) operator failure (for example due to clear artifacts due to objects in the field of view, wrong positioning of head, wrong acquisition protocol, severe motion artifacts, missing reconstructions) or (b) technical failure due to missing calibration of the scanner. The ultimate decision to exclude cases is made by the Independent Core Lab (under the supervision of [name]). In such a case it is the obligation of the Sponsor to perform retraining. Excluded cases will be replaced to ensure adequate power.

The imaging core-lab will use a standardized form to note all endpoints, in specific:

- Primary outcome:
  - Occurrence of an intracranial hemorrhage (yes/no)

The primary outcome will be assessed on both scans.

Only on the MDCT scans the following variables will be assessed as well:

- - Type of intracranial hemorrhage (SAH, intraparenchymal hemorrhage, intraventricular hemorrhage, subdural hemorrhage, epidural hemorrhage)
  - Is the intracranial hemorrhage isolated to the infratentorial region? (yes/no)

Only on the FDCT scans the following variables will be assessed as well:

- - Was contrast-media present at the evaluation of the scan? (yes/no)
  - If yes, did it enhance your capability to detect/exclude a hemorrhage? (yes/no)

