### 11.5.2 Primary Analysis

The primary analysis will be based on the FAS. As described for the sample size calculation, a generalized linear random-effects model with a logit link function will be fit. The explanatory variables ’reader’ and ’patients’ will be random effects. Difficult cases will be weighted with 2%. From the fixed-effect intercept of sensitivity and specificity, the 95%-CIs will be calculated applying the method of Wald. Sensitivity will be calculated based on the results of all core-lab readers of the non-contrast syngo DynaCT Sine Spin scans of all patients for which the ground truth was deemed to be hemorrhage positive. Specificity will be calculated based on the results of all core-lab readers of the non-contrast syngo DynaCT Sine Spin scans of all patients for which the ground truth was deemed to be hemorrhage negative. It will be tested whether both the lower bound of the 95%-CI of the sensitivity and specificity are higher than the margin of 95%.

All results will be reported in concordance with the STARD guidelines.^20^

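### The 2% weight for isolated infratentorial bleeds rests on their share of all suspected strokes; among haemorrhages, the denominator sensitivity uses, the protocol's figures point to roughly 4–6%

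*Protocol*

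**What the plan says.** Section 6.1 (reason 2) requires 14 patients with isolated infratentorial bleeds, chosen because such bleeds were harder to see on earlier FDCT systems. It notes that they make up 11% of the 126 bleeding cases, and then states that "they will contribute to the estimate of the sensitivity for the detection of intracranial hemorrhage of FDCT with a fixed weight of 2" percent. Two supports are given. One is the investigators' experience that such cases are under 1% of the investigated population and seldom present in a way that would lead to direct angiography. The other is a registry check of 5,448 suspected strokes: "Out of these only 48 patients (0.8%) presented with an isolated infratentorial bleeding".

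Section 11.5.2 repeats the rule ("Difficult cases will be weighted with 2" percent). It computes sensitivity from the FDCT readings "of all patients for which the ground truth was deemed to be hemorrhage positive". The success rule is: "It will be tested whether both the lower bound of the 95%-CI of the sensitivity and specificity are higher than the margin of 95" percent.

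On how common haemorrhage is, section 3.4.2 reports that "in our targeted patient population (suspected acute stroke patients with an NIHSS ≥7) 16% presented with such a spontaneous haemorrhage", and section 3.1 gives 15–20% of severely affected stroke patients.

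The bucket in section 6.1 that supplies the 14 patients is wider than the registry count: "isolated infratentorial or basal intracranial haemorrhage including perimesencephalic SAH".

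**The concern.** A weight inside a sensitivity estimate is a share of haemorrhages, because only haemorrhages enter that estimate. Both supports for 2% are shares of all suspected strokes, most of which are ischaemic. Section 6.1 does use the haemorrhage denominator when it contrasts the weight with 14 of 126, so one paragraph sets a share of bleeds beside a share of strokes.

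Too small a weight makes the primary sensitivity less responsive to the stratum the protocol itself regards as hardest for FDCT, and the error runs in favour of success. Section 11.5.3 reports sensitivity in this subset separately, but no success criterion is attached. A poor subset result therefore could not by itself stop a non-inferiority claim.

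**Working it through.** **Inputs.** 48 and 5,448 (section 6.1); haemorrhage share 16% (3.4.2) and 15–20% (3.1); total weight 0.02, sensitivity 99% and 70% in difficult cases, 6 readers, 238 evaluable patients at 1:1 (11.2). This gives 119 evaluable haemorrhages, or 119 − 14 = 105 others if no difficult case drops out. The reader correlation is described only as high, so a range is used.

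**Step 1: the plan's own figures.** 48/5,448 = 0.881%, which rounds to 0.9% (printed as 0.8%). 14/126 = 11.1%, as printed.

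**Step 2: share among haemorrhages** = 0.881% / haemorrhage share.
- At 15%: 5.9%. At 16%: 5.5%. At 20%: 4.4%. Using the printed 0.8% instead: 5.3%, 5.0% and 4.0%.
- Over a wider assumed range, 10% to 25%: 8.8% to 3.5%.
- For 2% to be right, haemorrhage would have to be 0.881%/0.02 = 44% of suspected strokes.

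**Step 3: weighted sensitivity**, Se = (1−w)·Se_other + w·Se_difficult.
- On plan (99%, 70%): w = 2% gives 0.98×0.99 + 0.02×0.70 = 98.4%; w = 5.5% gives 0.945×0.99 + 0.055×0.70 = 97.4%.
- All difficult bleeds missed, 99% elsewhere: w = 2% gives 0.98×0.99 = 97.0%; w = 4.4% gives 94.6%; w = 5.5% gives 93.6%.
- All missed, 100% elsewhere: 98.0%, 95.6% and 94.5% respectively.

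**Step 4: the lower bound**, since the rule concerns the bound and not the point estimate. Take w = 2%, all 14 missed by all readers, 99% in the other 105, and reader correlation ρ. Then SE = 0.98·√[0.99×0.01/105 × (1+5ρ)/6]; the difficult stratum adds no variance when none is detected. At ρ = 0.2, SE = 0.00549. On the logit scale this is 0.00549/(0.9702×0.0298) = 0.190, and 3.483 − 1.96×0.190 = 3.11, which transforms back to 95.7%.

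| ρ | Plain Wald bound | Logit-Wald bound |
|---|---|---|
| 0.05 | 96.2% | 96.0% |
| 0.2 | 95.9% | 95.7% |
| 0.4 | 95.7% | 95.4% |
| 0.6 | 95.5% | 95.1% |
| 0.8 | 95.3% | 94.8% |
| 1 | 95.2% | 94.5% |

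At w = 5.5% no bound can exceed 95%, because the point estimate is at most 94.5%. At w = 4.4% a pass is only just possible: with one missed reading out of 630 among the other bleeds, the logit-Wald bound is 95.1% at ρ = 0.05 and 94.9% at ρ = 0.4.

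**Step 5: simulation, as an indication.** With all 14 missed and ρ from 0.05 to 0.6, the weighted marginal estimate at 2% met the sensitivity criterion in 46–67% of runs, and at 5.5% in none. The intercept of an approximate version of the planned mixed model (patient random effect only) still met it in 99–100% of runs at 5.5%. That intercept describes a typical patient, and the patient effect absorbs the fully missed cases. The exact rates depend on how the weight enters the likelihood.

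**The case against.** **The 5.5% is not a protocol figure.** This stands. The 48/5,448 covers all suspected strokes, while the 16% covers NIHSS ≥ 7 and refers to intraparenchymal or intraventricular bleeds. The haemorrhage share within the 5,448 is not given. If subarachnoid bleeds are added using the trial's expected mix in section 3.7 (40–45% and 5–10% of subjects), 16% becomes about 17.8–20% and the share about 4.4–5.0%. A reader might infer that 5.5% is the correct replacement weight; the document supports only roughly 4–6%.

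**Rare presentation for direct angiography.** This could justify a weight below the registry share in the intended-use population, and 2% already exceeds the investigators' own estimate of under 1%. But the remark carries no figure, and the registry check offered to validate the rarity uses the wrong denominator.

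**A total miss would be visible.** It would, in the separate subset report, for which section 6.1 plans 80% power to exclude 50%. It would not change the primary verdict.

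**Readings that go too far.** A reader might take the wording in section 11.5.2 to mean 0.02 per case, but section 11.2 sets a total weight of 0.02 and 11.5.2 refers back to it. A reader might also infer that basal or perimesencephalic bleeds would escape down-weighting, because the core-lab item in section 9.2 asks only about the infratentorial region. No section says which variable assigns the weight; bleed location is also entered at enrolment. What remains is that the bucket, the registry count and the difficult-case definition do not match.

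**Conclusion.** The point holds in this form: the weight is justified on a denominator that does not belong to the estimate, and no figure in the protocol supports 2%. On the protocol's 15–20% haemorrhage share, the share among bleeds is roughly 4–6%, or 2.2 to 2.9 times the weight used. This assumes that share carries over to the registry's 5,448 patients; at an assumed 10–25% the result is 8.8–3.5%, still above 2%.

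On plan, the effect is about one percentage point (98.4% against 97.4% at 5.5%). At the extreme, the sensitivity criterion could be met with every difficult bleed missed. That needs about 99% sensitivity elsewhere and, under the logit-Wald bound, a reader correlation up to about 0.6. A reader might infer that the trial would pass in that event. The calculations show only that it could, and the protocol's unspecified high correlation may lie on either side of that limit. Nor should a reader conclude that changing the number is enough, since the mixed-model intercept may still pass with a corrected weight.

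Because the rule feeds a co-primary criterion and errs towards success, it should be corrected before database closure.

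**What to change.** 1. In sections 6.1, 11.2 and 11.5.2 (and the synopsis), set the total weight w to the registry count of difficult bleeds divided by all haemorrhages in the same registry population. If the intended-use population justifies a lower value, give the count that shows it.
2. Use one definition of difficult case (isolated infratentorial only, or also basal and perimesencephalic bleeds) for bucket 3, the registry count and the analysis, and name the variable that assigns it.
3. Apply w to a marginal stratified estimate, Se = (1−w)·Se_other + w·Se_difficult, with a stratified variance that allows for correlated readings, in place of case weights in the mixed model.
4. Keep w = 2% as a sensitivity analysis, and correct the printed 0.8% to 0.9%.

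The cost is one registry count and wording changes in a few sections. Planned sensitivity falls from about 98.4% to about 97.4% at w = 5.5%, so some power is lost. The 90% power should be recomputed and restated for the chosen weight and estimator, with the assumed reader correlation given.
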